#### Treatment and study evaluation interview

A semi-structured interview developed based on Krause et al. [111] will be used to assess how patients experienced the therapy and the study, what aspects they perceived as positive or negative, and what impact the therapy had on their symptoms and their life.

### Power calculations and sample size

In an RCT of MBT vs. structured clinical management (SCM), Bateman and Fonagy [19] encountered a mean count of 1.8 cases of critical behaviour in MBT vs. 2.6 cases in the SCM group at 12 months of treatment, resulting in a relative risk of 0.7. In another randomized controlled study of MBT vs. standard psychiatric care [18], the median count of self-mutilation in a 6-months period was reduced from 9 to 1 in MBT and from 8 to 6 in standard psychiatric care. As we expect our comparator to be more effective than the comparators used in the previous studies, we are raising the relative risk in order not to overestimate the effect of MBT. Accordingly, we assume 10 events per patient in the control group and 7.5 cases in the MBT group for the whole 24-months period, and would rate a relative risk of 0.75 [112] as sufficiently relevant requiring a model setting as described below to successfully reject the null hypothesis of no effect. As a more conservative approach, we assume less events (but the same relative risk), i.e. 5 events in the control group per patient and 3.75 in the treatment group. Therefore, a log-linear model (Poisson regression) with treatment as explanatory variable, and number of crisis events in 24 months as response, with a mean of 5 events expected for the BFT and 3.75 for the MBT group, results in a relative risk of 0.75. A test of the null hypothesis “no association between treatment and primary endpoint” at α = 0.05 level rejected with a power of 78% if 8 patients could be enrolled per cluster and 38 clusters could be randomized simulated with R assuming a dropout rate of r = 30% and an intraclass-correlation coefficient of 0.1 (ICC). The dropout rate is taken into account using the correction factor of 1/(1-r)^2 according to [113]. The sample size was corrected with help of the ICC according to [114].

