### Primary analysis

The purpose of this trial is to show whether the (incidence) rate of crisis events (suicides, suicide attempts, self-harm behavior recorded throughout therapy and up to 12 month after therapy) is lower for BPD-patients undergoing MBT than for BPD-patients undergoing a BFT. The null-hypothesis (H01) to be tested can be formulated as follows: The (incidence) rates of crisis events in the MBT and in the BFT group are the same. A log-linear (Poisson) regression model (GLMM) will be used to fit with treatment group, sex and age as explanatory variables, along with log of observation (treatment + follow-up) time as an offset. The randomization cluster will be considered as random effect. Poisson regression lends itself to analysis of count data, considering that more events of suicidal behavior within a time frame are worse than one, and controlling for the period of observation by using it as an offset in the model. The null hypothesis (H01) of no treatment effect will be tested using Wald type tests on the regression coefficient of the treatment group (MBT vs. BFT). Tests will be two-sided at the 0.05 level.

Missing values will be replaced using multiple imputation using fully conditional specification methods (FCS) considering randomization cluster, sex, age and the respective value over time.

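### The stated 78% power makes no allowance for patients differing in event rate, and the primary Poisson model has no patient-level variance term

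*Protocol article*

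**What the plan says.** Under 'Power calculations and sample size', the protocol article first considers a more favourable case, in which "we assume 10 events per patient in the control group and 7.5 cases in the MBT group for the whole 24-months period". It then takes a more cautious case for the calculation: "Therefore, a log-linear model (Poisson regression) with treatment as explanatory variable". That cautious case is specified "with a mean of 5 events expected for the BFT and 3.75 for the MBT group, results in a relative risk of 0.75". The null hypothesis, according to the article, is "rejected with a power of 78% if 8 patients could be enrolled per cluster and 38 clusters could be randomized simulated with R". The calculation allows for 30% dropout and an ICC of 0.1. Dropout enters through a factor 1/(1−r)², and the sample size is also corrected for the ICC. The section gives no standard deviation, dispersion parameter or overdispersion allowance for the counts.

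Under 'Primary analysis', the model is a Poisson GLMM with treatment, sex and age as covariates and log observation time as offset. On random effects it says: "The randomization cluster will be considered as random effect". It names no patient-level random effect, negative-binomial model or robust variance. The treatment coefficient is tested by a Wald test, and "Tests will be two-sided at the 0.05 level".

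**The concern.** A Poisson model in which cluster is the only other source of variation says that all patients in the same arm and cluster share one event rate, apart from sex and age in the analysis model. With a mean of 5 over 24 months, that implies that about 0.7% of control patients have no event (e⁻⁵ = 0.0067) and about 1.4% have more than 10.

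This is hard to believe for the outcome described. It pools suicide, suicide attempts and every act of self-harm, and patients report how often each occurred. Eligibility requires repeated behaviour with at least one occurrence in the past six months, and sets no upper limit. Patients who self-harm rarely and patients who do so often will be in the same arm.

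What is at stake is how the result is read. The Discussion presents adequate powering as an advantage over former trials. If the true chance of detecting a rate ratio of 0.75 is well below 78%, a null result would be taken as stronger evidence against a difference than it is.

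**Working it through.** **Inputs from the protocol article:** 304 patients (38 clusters of 8), 1:1 allocation, means 5 and 3.75, rate ratio 0.75, ICC 0.1, dropout r = 0.30 with factor 1/(1−r)², two-sided α = 0.05.

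**Assumed:** the ICC correction is the usual design effect, 1 + (8 − 1) × 0.1 = 1.7, since the article gives only the ICC. The dispersion k, with variance μ + kμ², is not given, so a range is shown.

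**Step 1: reproduce the stated power.**
- Effective patients per arm: 304 × 0.49 / 1.7 / 2 = 43.8.
- SE² of the log rate ratio: (1/5 + 1/3.75) / 43.8 = 0.01065, so SE = 0.103.
- |ln 0.75| / SE = 0.2877 / 0.103 = 2.79.
- Power = Φ(2.79 − 1.96) = 79.6%. A t reference with 36 degrees of freedom gives 77.4%.

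This agrees with 78%. Other readings do not: dropout counted as (1−r) gives 91.5%, no dropout 97.8%, and no design effect 95.3%.

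**Step 2: add between-patient dispersion to the same formula.** SE² becomes (1/5 + 1/3.75 + 2k) / 43.8.

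**Step 3: simulate the planned analysis.** Step 2 keeps the plan's dropout factor, which retains 49% of the information. The planned offset model is milder, because a patient who leaves early still contributes events and time. The simulation used:
- 38 clusters of 8, with 30% of patients leaving in year 1 and contributing partial time;
- a Poisson GLMM with a cluster random effect only;
- cluster variance 0.022, which is ICC 0.1 at mean 5: 5 × (0.1/0.9) / 25 = 0.022.

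Where the table shows a range, it covers separate sets of runs.

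| k (assumed) | Control variance ÷ mean (1 + 5k) | Power, plan's corrections | Power, simulated offset GLMM |
|---|---|---|---|
| 0 | 1 | 79.6% | about 95% |
| 0.1 | 1.5 | 64% | not run |
| 0.2 | 2 | 53% | 85–87% |
| 0.5 | 3.5 | 35% | 67–70% |
| 1 | 6 | 23% | 48–54% |
| 2 | 11 | 15% | 31–34% |

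In one set of simulations, power at k = 0.4 was 73.5%. Interpolating between k = 0.2 and 0.4 puts 78% at k of about 0.3.

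**Step 4: sensitivity.**
- *Larger means.* With 10 and 7.5 events and the plan's corrections, power is 67% at k = 0.2, 40% at 0.5 and 25% at 1. More events help little once k dominates the variance.
- *Reading of the ICC.* If 0.1 is taken as the cluster variance on the log scale and 30% of patients are lost entirely, simulated power is 62% at k = 0, 49% at 0.5, 36% at 1 and 23% at 2. The level depends on the reading, but the decline with k does not.

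**Step 5: the treatment test under the null.** Simulated size was roughly 5–8% with no clear trend in k. One set of 600 runs per setting gave 7.2% at k = 0 and 7.2% at k = 2. Treatment is constant within a cluster, so the cluster random effect takes up most of the excess variation. It does not do so for covariates that vary within clusters: with k from 1 to 4, an age covariate with no true effect was significant in 41–66% of runs.

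**The case against.** The strongest objection is that the documents give no dispersion value, so the size of any loss is assumed. That stands. The cited trials do not supply one either. One reports means of 1.8 and 2.6 at 12 months. In the other, "the median count of self-mutilation in a 6-months period was reduced from 9 to 1 in MBT" and from 8 to 6 under the comparator. These are differences between trials, on different outcomes, partly before and partly after treatment. A reader might infer a particular within-arm spread from them, but they do not measure it.

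A reader might also infer that 78% cannot be reached with any patient-level variation. That does not follow. The plan's dropout factor is harsher than the offset analysis it precedes, and this leaves room for k up to about 0.3. The two columns of the table also start from different baselines, so they should not be merged into one headline range.

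A further tempting reading is that the primary test is invalid because the model omits overdispersion. Step 5 does not support this. The hypothesis test concerns only the treatment coefficient, and its size shows no dependence on k. The standard errors for sex and age would be wrong, but they do not bear on the primary hypothesis.

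Finally, the article refers to a separate statistical analysis plan, which may contain overdispersion checks, and a negative-binomial model would not recover power lost to real heterogeneity. Both remarks are fair. However, the article itself prints the power figure and fixes the model. The gain from the change is an honest statement of power and of patient-level variance, not more power.

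**Conclusion.** The concern holds as a statement about robustness. The 78% matches the plan's formula with no patient-level heterogeneity, and that formula falls quickly once any is added: to 53% when the control variance is twice the mean (k = 0.2) and 35% when it is 3.5 times the mean (k = 0.5). Under the planned offset analysis with partial follow-up, the decline starts from about 95%, passes 78% near k = 0.3 and reaches about half at k = 1.

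These figures rest on an assumed k, an assumed design effect of 1.7 for the first set, a cluster variance of 0.022 for the second, and the protocol's event means taken as given. The direction is the same under every reading tried. The fixed primary model also has no patient-level term, so it understates patient-level variance, although the treatment test is largely protected.

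**What to change.** 1. Re-run the R simulation under the planned offset analysis with stated patient-level dispersion, for example k from 0.2 to 2. State how the ICC is translated into a cluster variance and how dropouts contribute time. Replace the single 78% with the resulting range.
2. Specify a negative-binomial mixed model, or add a patient-level random intercept to the Poisson GLMM. Keep the cluster random effect and the log-time offset. Make the choice before unblinded analysis, so that it is not a post hoc switch.

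The cost is a re-run simulation, a small change to the model specification and a less favourable stated power. No extra patients are required.

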### Primary outcome

#### Crisis events – composite outcome

The primary outcome of the study is the incidence of crisis events as indicated by 1) suicides, 2) suicide attempts, or 3) self-harm behavior.

To assess suicide attempts and self-harm behavior, the following four questions taken from the Self-Harm Behaviour Questionnaire ([53], German version: [54]) will be used: “Have you ever intentionally hurt yourself or caused yourself pain? (e.g. scratched with fingernails or with other sharp objects?)”, “How often have you intentionally hurt or caused yourself pain?”, “Have you ever tried to take your own life?” and “How often did you try to take your own life?”. These questions will be adapted for the Ecological Momentary Assessment (e.g., “Since the last signal have you ever intentionally hurt or caused yourself pain? (e.g., scratched with fingernails or with other sharp objects?”). Only if any of the crisis events occurred, the patient will be asked to indicate the frequency of the event(s).

Crisis events like suicides cannot be reported by the patient themselves but should be taken into account as well (see e.g. Bateman and Fonagy [18]). Suicides are recorded via the Serious Adverse Events (SAE) reports.

To increase ecological validity, the incidence of crisis events 1) – 4) will be assessed during one week each month over the course of 12 months of treatment, and one week every three months post treatment up to the 12-month-follow up (T3). During the assessment week, patients will be asked to complete one online-assessment every other day, resulting in 4 assessments per assessment week.

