In addition, the trial offers the unique opportunity to overcome methodological limitations of former trials by sufficient sample powering, use of valid measures as well as investigating cost-effectiveness, adverse events and side effects of treatment. MBT is a manualized treatment with feasible training and supervision demands. A broad national dissemination and with this potentially improve routine care of BPD patients in Germany represents a key ultimate goal of the study.

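### The 78% power counts crisis events over the full 24 months, but self-harm and suicide attempts are assessed in only 16 of about 104 weeks; if the items cover only those weeks, power on the same inputs is about 19–28%

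*Protocol article*

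**What the plan says.** All references are to the protocol article.

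- **Power calculations and sample size** first sets the event rates: "we assume 10 events per patient in the control group and 7.5 cases in the MBT group for the whole 24-months period". As a more conservative case it halves both, with the "number of crisis events in 24 months as response, with a mean of 5 events expected for the BFT" arm and 3.75 for MBT, which "results in a relative risk of 0.75". With 38 clusters of 8, an ICC of 0.1, 30% dropout and a correction factor of 1/(1−r)², the null hypothesis is "rejected with a power of 78" per cent. One of two cited benchmarks is "a mean count of 1.8 cases of critical behaviour in MBT vs. 2.6 cases in the SCM group at 12 months of treatment". The other is a median self-mutilation count over 6 months that fell from 8 to 6 under standard psychiatric care.
- **Crisis events – composite outcome** says that incidence "will be assessed during one week each month over the course of 12 months of treatment, and one week every three months post treatment", with four prompts per assessment week. The Abstract and the note to Table 1 give the same schedule. The sample item asks about the time since the previous prompt. Suicides alone are picked up outside EMA, through serious adverse event reports.
- **Primary analysis** states: "Tests will be two-sided at the 0.05 level".
- **Discussion** says the trial can "overcome methodological limitations of former trials by sufficient sample powering".

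**The concern.** The precision of a Poisson rate comparison is set by the number of events counted, not by the number that occur. The power section uses a 24-month total, while the outcome section counts self-reported events in a small sample of weeks. Nothing in the power section links the two.

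At stake is the reading of the primary result. A trial believed to have 78% power but holding far less would probably miss a true rate ratio of 0.75. The null result could then be taken as evidence that MBT is not superior.

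**Working it through.** **Inputs, all from the protocol article.** 304 patients, 1:1, so 152 per arm. Clusters of 8 and ICC 0.1. Dropout r = 0.30 with factor 1/(1−r)², so 0.49 of the sample is effective. Two-sided α = 0.05. Rate ratio 0.75, ln 0.75 = −0.2877.

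**Formula.** Effective n per arm = 152 × 0.49 / [1 + (8−1) × ICC]. SE(log RR) = √[(1/μ₀ + 1/μ₁)/n]. Power = Φ(0.2877/SE − 1.96).

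**Step 1: reproduce the 78%.**
- Design effect = 1 + 7 × 0.1 = 1.7, so n = 74.48/1.7 = 43.8 per arm.
- Means 5 and 3.75: SE = √[(0.2000 + 0.2667)/43.8] = 0.103, z = 2.79, power 79.6%.

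This is within 2 points of the stated figure. Plausible variants miss it: 87.3% one-sided, 91.5% with dropout as (1−r), and 97.6% at 10 versus 7.5 events. So the 78% corresponds to 5 versus 3.75 events, all of them counted.

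**Step 2: sampled fraction.** Year 1 gives 12 weeks and year 2 gives 4. 16/104 = 0.154, or 1 in 6.5.

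**Step 3: captured means, if only the assessment weeks count and events are spread evenly.**
- 5 and 3.75 become 0.769 and 0.577.
- 10 and 7.5 become 1.538 and 1.154.

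**Step 4: power with ICC 0.1 kept.**
- 0.769 and 0.577: SE = √[(1.300 + 1.733)/43.8] = 0.263, z = 1.09, power 19%.
- 1.538 and 1.154: SE = √[(0.650 + 0.867)/43.8] = 0.186, z = 1.55, power 34%.

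**Step 5: power with the between-cluster rate variance held fixed.** Counting fewer events from the same process leaves the rate variation between clusters unchanged, so the ICC on the count scale falls. With k = ICC/[(1−ICC)μ], an ICC of 0.1 implies k = 0.0222 at μ = 5 or 0.0111 at μ = 10. The new ICC is kμ/(1+kμ).

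| Control events in 24 months | k | New ICC | Design effect | n per arm | SE | Power |
|---|---|---|---|---|---|---|
| 5 | 0.0222 | 0.0168 | 1.118 | 66.6 | 0.213 | 27% |
| 5 | 0.0111 | 0.0085 | 1.059 | 70.3 | 0.208 | 28% |
| 10 | 0.0222 | 0.0331 | 1.231 | 60.5 | 0.158 | 44% |
| 10 | 0.0111 | 0.0168 | 1.118 | 66.6 | 0.151 | 48% |

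A Poisson-gamma cluster simulation (4,000 replicates, 0.49 retained) gave 26–29% at 5 events and 47–50% at 10.

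**Step 6: what would keep 78%.** With ICC 0.1 and the plan's dropout factor, the captured control mean must be (1.960 + 0.772)² × (1 + 1/0.75) / (0.2877² × 43.8) = 4.8. Dividing by 0.154 gives about 31 true events per control patient in 24 months, against the 5 to 10 assumed.

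**Step 7: uneven timing.** Year 1 is sampled more densely. In the extreme case that every event falls in year 1, capture is 12/52 = 23.1% and the means are 1.154 and 0.865. SE = √[(0.867 + 1.156)/43.8] = 0.215, z = 1.34, and power at the 5-event rate is still only 27% with ICC 0.1 kept.

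**The case against.** **The look-back may cover the gaps.** The sample item asks about the time since the previous prompt. Taken literally, the first prompt of a week reaches back to the previous assessment week, and capture would be nearly complete. This stands as a condition on the result. But the item is given only as an example of adapted wording, the section places assessment within one week at a time, and the gaps are about 3 weeks in year 1 and 12 in year 2. Recall that long sits badly with the section's stated aim of ecological validity.

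**Five may already mean captured events.** The power section calls it the mean of the model response. The wording does not support this reading: the parent figure of 10 is tied to the whole 24 months, and the response is events in 24 months. The halving is described only as more conservative, and it is a factor of 2 where the schedule implies 6.5. The cited 2.6 at 12 months, if it is a 12-month total, doubles to 5.2 and fits a full-period count. The article does not say that it is such a total.

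**True rates may be higher.** Six acts per 6 months, taking the median as a mean and the rate as constant, is 24 in 24 months, or 3.7 captured. Power is then about 67% with ICC 0.1 kept. With the k values of step 5 it is 71–79%. The pre-treatment 8 per 6 months (32 in 24 months) gives 79% with ICC 0.1. This stands as a reason not to predict the trial's actual power. It does not rescue the stated figure, because the plan did not power on those rates and expects a more effective comparator.

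**The dropout factor is harsh.** With (1−r) instead, the results are 26–38% at 5 events and 46–63% at 10. That variant does not reproduce the 78%.

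**Conclusion.** The stated 78% does not follow from the plan's own event rates and assessment schedule. At the 5-event rate on which it rests, power is about 19% with ICC 0.1 kept, or 27–28% with the cluster rate variance held fixed. At the 10-event rate it is about 34%, or 44–48%, and there the like-for-like comparison is about 98%.

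This rests on three assumptions: the EMA items cover only the assessment weeks, events are spread evenly over time, and patients show no extra-Poisson variation, as in the plan's Poisson model. Overdispersion would lower every figure. Suicides from adverse event reports add too few events to matter.

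Two stronger readings are tempting. A reader might set one range of roughly 20–45% against the 78%, but the upper part of that range needs the 10-event rate, so it is not like for like. A reader might also conclude that the trial will certainly be underpowered. The article leaves the look-back undefined and cites a benchmark with a higher event rate, so it supports only the conditional statement.

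**What to change.** 1. In the composite outcome section, state the period that the first prompt of each assessment week refers to.
2. In the power section, say that 5 versus 3.75 are events occurring over 24 months, derive the events expected inside the windows actually covered, and recompute power on those. State whether the ICC or the between-cluster rate variance is carried over.
3. Replace the 78% with the result, and qualify the Discussion's claim about powering to match.

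The cost is a recalculation and some wording. The downside is that the stated power becomes less favourable, unless a look-back across the gaps is what is meant. Asking for event counts at T1, T2 and T3 is not part of this fix: it would need recall over 6 to 12 months, and as a supportive endpoint it would restore no power to the primary analysis.

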### Compliance/rate of loss to follow-up

Building on similar trials comparing MBT with BFT for BPD patients we expect a compliance rate of about 70%, with Bateman and colleagues [19] achieving 99/134 = 73% compliance over 18 months and Jorgensen and colleagues achieving 63/85 = 74% compliance over 24 months [20]. Both Poisson regression for analyzing the primary outcome and multilevel models for analyzing the secondary outcomes handle unbalanced data with different number of measurements per person [115]. As such, the intent-to-treat sample is used in all analyses instead of complete cases.

### Statistical analysis

All analyses will be specified in a statistical analysis plan.

### Primary analysis

The purpose of this trial is to show whether the (incidence) rate of crisis events (suicides, suicide attempts, self-harm behavior recorded throughout therapy and up to 12 month after therapy) is lower for BPD-patients undergoing MBT than for BPD-patients undergoing a BFT. The null-hypothesis (H01) to be tested can be formulated as follows: The (incidence) rates of crisis events in the MBT and in the BFT group are the same. A log-linear (Poisson) regression model (GLMM) will be used to fit with treatment group, sex and age as explanatory variables, along with log of observation (treatment + follow-up) time as an offset. The randomization cluster will be considered as random effect. Poisson regression lends itself to analysis of count data, considering that more events of suicidal behavior within a time frame are worse than one, and controlling for the period of observation by using it as an offset in the model. The null hypothesis (H01) of no treatment effect will be tested using Wald type tests on the regression coefficient of the treatment group (MBT vs. BFT). Tests will be two-sided at the 0.05 level.

Missing values will be replaced using multiple imputation using fully conditional specification methods (FCS) considering randomization cluster, sex, age and the respective value over time.

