**Methods:**

Across 5 study sites in Germany, 304 individuals of all genders from age 18 to 65 with a BPD diagnosis and NSSI or suicide attempts in the past will be asked to participate in the study for a period of two years. In the first year, patients will receive either MBT or BFT and will take part in continuous scientific assessments. Scientific assessments will continue after therapy completion up to a 12-month follow up. As primary outcome, crisis events will be assessed via ecological momentary assessment (EMA) in one week per month (four weekly assessments) during the first year, and in one week every three months during the second year. Number of crisis events up to 2 years post randomization will be compared between treatment arms using a log-linear regression model following an intention-to-treat approach. Secondary outcomes and mediator variables will be assessed at several timepoints.

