To investigate efficacy of MBT versus BFT, a total of *n* = 544 patients with a BPD diagnosis will be screened for eligibility at five study sites in Germany: University Hospital Heidelberg (Institute for Psychosocial Prevention, ST, and Department of General Psychiatry, SHe), University Hospital Jena (Institute for Psychosocial Medicine, Psychotherapy and Psychooncology, BS), University Hospital Düsseldorf (Clinic for Psychosomatic Medicine and Psychotherapy, UDE & JR), University Hospital Ulm (Clinic for Psychosomatic Medicine and Psychotherapy, HG, JV), Psychologische Hochschule Berlin (Department of Clinical Psychology and Psychotherapy, TS). Of the patients screened, *n* = 304 are expected to fulfil all inclusion criteria including informed consent to participate in the trial, to complete the baseline assessment (T0) and to be allocated to the trial (Fig. 1). Patients will be randomized in groups of 8 (randomization cluster) in a 1:1 ratio to either MBT or BFT using block randomization. Randomization will be stratified by study site. For randomization, study site coordinators will use a centralized web-based tool (randomizer.at) to maintain allocation concealment. Role-based user rights ensure that only approved study personnel may perform randomizations. Main assessments will be conducted for both arms at 6 months (in-therapy assessment, T1), at 12 months (T2) and at 24 months after start of therapy (12-months follow-up, T3). A final sample of *n* = 304 is expected to be obtained for data clearance and analysis using an intent-to-treat protocol. A drop-out of 30% during therapy is expected and acknowledged in our power analysis. Blinding of study team, trial personnel at site as well as patients is not feasible due to the nature of the interventions. Only central assessors will be blind to treatment. Allegiance bias is minimized as the consortium includes representatives of all trial treatments (MBT, group therapy, BFT).

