## Interventions

### MBT

Patients in MBT will receive a maximum of 58 sessions in total. Of those, 30 are weekly individual sessions. 28 sessions are weekly group sessions conducted by two therapists, and consisting of 8 introductory sessions of group psychoeducation (MBT-I) followed by 20 group therapy sessions. The duration of MBT is 12 months. The therapists, who must be specialized in PT and at least be in advanced psychotherapeutic training, will receive a 3-day training in MBT as well as an online course and supervision. MBT is manualized and relies on validating the emotional experience of patients that aims to promote mentalizing. The proposed mechanism of change in MBT is to stabilize mentalizing in certain focus areas in order to create a psychic buffer between affect and behaviour to foster affect regulation, reduce impulsivity and promote functional, supportive relationships.

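### The primary outcome window has three different anchors, and the primary analysis states the one that, read literally, depends on therapy length

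*Protocol article*

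**What the plan says.** The protocol article describes the period of the primary count in several places.

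- Abstract, Methods: "Number of crisis events up to 2 years post randomization will be compared between treatment arms". The same paragraph also says "Scientific assessments will continue after therapy completion up to a 12-month follow up" and sets the EMA calendar by study year: "in one week per month (four weekly assessments) during the first year, and in one week every three months during the second year".
- Aim, design and setting: the last main assessment is placed "at 24 months after start of therapy (12-months follow-up, T3".
- Crisis events – composite outcome: EMA runs "during one week each month over the course of 12 months of treatment, and one week every three months post treatment", ending at T3.
- Primary analysis: events are those "recorded throughout therapy and up to 12 month after therapy", and the Poisson model is fitted "along with log of observation (treatment + follow-up) time as an offset".
- Power calculations and sample size: the response is a 24-month count.

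Therapy length differs in kind between the arms. For MBT, "The duration of MBT is 12 months". For BFT, the Procedure section says that treatment may be shorter or longer than MBT (12 to 100 hours) and that the study does not control its length. The BFT section allows one or two sessions a week.

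**The concern.** The three anchors are randomization, start of therapy and end of therapy. They give the same window only if therapy starts at randomization and lasts exactly 12 months. Nothing in the article says which one governs, so two analysts working from different sections would build different primary datasets.

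The Primary analysis wording matters most because it defines both the count and the offset. Taken literally, observation ends 12 months after each patient's own therapy ends. Therapy length is determined after randomization, and by design it is free in BFT. A patient with a short BFT course would have EMA weeks collected before T3 that lie outside the window. A patient treated for more than 12 months would have a window running past T3, where no EMA is scheduled. An anchor at therapy start also depends on something that happens after randomization, and it leaves patients who never start without a window. Neither fits the planned intention-to-treat comparison well.

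A window that differs between patients does no harm in itself if the event rate is constant and the offset measures the time actually assessed. It can bias the rate ratio in three situations:

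- Event rates change over time.
- The offset is calendar time, while EMA is three times denser in year 1 than in year 2.
- Events collected up to T3 are paired with an offset based on therapy length.

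**Working it through.** **The plan's own figure.** Inputs from Power calculations and sample size: 38 clusters of 8 (304 patients), means of 5 and 3.75 events in 24 months, 30% drop-out with factor 1/(1−r)², ICC 0.1. Two-sided 0.05 is from Primary analysis.

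- Effective patients per arm: 304 × 0.7² / (1 + 7 × 0.1) / 2 = 43.8.
- Standard error of the log rate ratio: √[(1/5 + 1/3.75)/43.8] = 0.103.
- Power: Φ(0.2877/0.103 − 1.96) ≈ 0.80 (0.796 unrounded), against the simulated 78%.

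The figure is reproduced. It rests on a 24-month count, so a fixed 24-month window leaves it as it is.

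**Length of the literal window.** W = therapy months + 12, with 4.348 weeks per month and no breaks.

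| Course | Therapy (months) | W (months) |
|---|---|---|
| MBT, 12 months | 12 | 24 |
| BFT, 12 sessions, two a week | 1.4 | 13.4 |
| BFT, 24 sessions, weekly | 5.52 | 17.5 |
| BFT, 24 sessions at 2.5 a month | 9.6 | 21.6 |
| BFT, 48 sessions, weekly | 11.04 | 23.0 |
| BFT, 100 sessions, weekly | 23.0 | 35.0 |

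The rate of 2.5 a month is MBT's own pace, 30 individual sessions in 12 months. Without breaks, 30 weekly sessions would take only 30/4.348 = 6.9 months, so the no-break lengths are minimum lengths. EMA stops at T3, so no more than 24 months can be observed.

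**EMA weeks inside the window.** The full schedule has 12 + 4 = 16 weeks. For W up to 24, n = 12 + (W − 12)/3. A 24-session course gives 12 + 5.52/3 = 13.84 weeks (weekly) or 12 + 9.6/3 = 15.2 weeks (MBT pace). That leaves out 2.2 or 0.8 scheduled weeks.

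**Rate ratio MBT/BFT with no true difference.** Three assumptions are not in the document: half of BFT patients have a 24-session course, the other half have 24 months, and every MBT patient has 24 months.

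- *Constant rate, EMA-time offset:* 1.00 whatever the windows.
- *EMA-time offset, year-2 rate half that of year 1 (assumed):* MBT (12 + 4 × 0.5)/16 = 0.875. BFT at the weekly pace is (12.92 + 14)/(13.84 + 16) = 0.902, ratio 0.97. At the MBT pace it is (13.6 + 14)/(15.2 + 16) = 0.885, ratio 0.99.
- *Calendar-time offset, constant rate (assumed):* MBT 16/24 = 0.667. BFT is (13.84 + 16)/(17.52 + 24) = 0.719, ratio 0.93, or (15.2 + 16)/(21.6 + 24) = 0.684, ratio 0.97.
- *All BFT patients at the cited average of 48 sessions, weekly:* n = 12 + 11.04/3 = 15.68. Calendar offset: 0.667/(15.68/23.04) = 0.98. EMA offset with halved rate: 0.875/(13.84/15.68) = 0.99.

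Ratios below 1 favour MBT.

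**The case against.** The best defence is that therapy and follow-up name study phases common to both arms. The abstract places both treatments in the first year. Aim, design and setting gives both arms the same visits at 6, 12 and 24 months and labels the last one the 12-month follow-up. Cost-effectiveness analysis calls T2 the post-therapy assessment without distinguishing arms. The EMA calendar goes by study year, and the power basis is 24 months. On this reading the Primary analysis wording simply means T0 to T3. How observation time is computed can be left to the analysis plan, which is not shown.

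Much of this stands, and it makes a fixed 24 months the likely intention. It does not settle whether the 24 months run from randomization or from therapy start. Nor does it settle what the offset measures, since the article words it as treatment plus follow-up time although EMA samples that time unevenly. These are statements in the article that do not agree, rather than details deferred to another document.

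A reader might go further and infer three things that the document does not support:

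- *That the windows will in fact differ between arms, or that collected EMA weeks will be discarded.* No section says so, and the fixed calendar points the other way.
- *That only BFT is affected.* MBT's session number is a maximum, and 30% drop-out during therapy is expected, so literal windows would vary in MBT too. The scenarios above hold every MBT patient at 24 months and so partly build in their contrast.
- *That the bias is large.* Pairing a 24-month count with a therapy-length offset gives a null ratio of 17.5/24 = 0.73 or 35/24 = 1.46. This requires every BFT patient to share one extreme length and the offset to mismatch the count, while in Primary analysis the two match.

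**Conclusion.** The inconsistency is real and should be corrected before analysis. The article's rules for the window cannot all hold once therapy starts after randomization or lasts other than 12 months. A fixed 24-month window was probably meant. The Primary analysis text nevertheless states a window and offset that, taken literally, follow therapy length: uncontrolled by design in BFT, and variable in MBT through drop-out.

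The size of any bias cannot be determined from the document. There is none with a constant rate and an EMA-time offset. In the scenarios above the null rate ratio is 0.93 to 0.99, which rests on the literal reading, on assumed BFT lengths and, depending on the scenario, on an assumed fall in event rate or a calendar-time offset. The lowest value needs the calendar-time offset. The gap between randomization and therapy start is not given, so the effect of that choice of anchor cannot be sized either. The stated power and the sample size of 304 are unaffected.

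**What to change.** In Primary analysis, define the count as all crisis events from randomization to 24 months after randomization in both arms, whatever the start or length of therapy. Define the offset as the time actually covered by completed EMA assessments within that window, in place of calendar treatment plus follow-up time. Align Aim, design and setting and Crisis events – composite outcome to the same anchor. State that patients who start therapy late or never start remain in follow-up. Where EMA has already been dated from therapy start, treat the uncovered early period as unobserved time and do not reschedule assessments.

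This agrees with the abstract, the power basis and the intention-to-treat approach, and needs no new patients or assessments. It has two costs. Waiting time before therapy counts in both arms and may slightly dilute the contrast. Where EMA was dated from therapy start, late weeks fall outside the window, about one EMA week for every three months between randomization and therapy start. Simply ending the count at T3 would avoid that loss, but it would keep an anchor that depends on a post-randomization event.
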